### Study Protocol Design

The present clinical study protocol describes a single-blind randomized controlled trial comparing 4 weeks of RAT using the NEEM robotic elbow exoskeleton to a control group receiving a matched volume of conventional physiotherapy. The primary outcome measures are the Modified Ashworth Scale (MAS) and the upper-extremity Fugl-Meyer Assessment (FMA) scale, two standard clinical scales used to assess upper-limb spasticity and functionality in neurological patients. Subjects are randomly assigned either to the control group (CG), or to the treatment (robotic) group (TG). Both groups will receive a conventional 4-week upper-limb physiotherapy program, consisting of repeated elbow flexion/extension movements: control group patients will focus on manual mobilizations of the limb while aided by the therapist, while the robotic group will receive the same net treatment volume via the robotic device. The treatment group will be further divided into two levels (sub-groups), based on pathological severity: Level 1 corresponds to an FMA score equal or below 28, and Level 2 with FMA >28. The two sub-groups will receive different combinations of robotically assisted *passive* and *active* mobilization treatment modalities, according to their differing clinical needs. Level 1 therapy is designed for patients with very low residual mobility, focusing on *passive mobilization* of the affected limb using a *robot-in-charge* control paradigm (29), where the robot moves the user's arm through a pre-defined spatio-temporal trajectory without requiring his/her active contribution, so as to entrain desired movement patterns and/or reduce joint stiffness (including spasticity). In addition to passive mobilization, Level 1 participants will also perform a limited number of *active mobilization* exercises, using a *patient-in-charge* paradigm (29) in which the user initiates and follows defined movement trajectories, receiving robotic assistance only *as-needed*. According to their higher motor function at baseline, Level 2 subjects will perform a greater proportion of active mobilizations relative to passive exercises (3:1), to emphasize the development of upper limb strength and motor control. Subjects in both treatment sub-groups will also be evaluated for their voluntary movement capacity in each session, via a brief bout of active movements performed with the robotic device in *transparent* (unassisted) mode.

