### Participants and Recruitment

All procedures conform to the Declaration of Helsinki and have been approved by the Ethical Committee for the Azienda USL Toscana Nord Ovest (AUSLTNO) and the Italian Ministry of Health.

The study is conducted at the Recovery and Functional Rehabilitation department of Ospedale Versilia (Lido di Camaiore, Italy), in collaboration with The BioRobotics Institute of Scuola Superiore Sant'Anna. It involves 60 post-stroke patients with right-sided hemiplegia, randomly allocated either to the control (*n* = 30) or treatment (*n* = 30) group. The sample size of each group was calculated based on the hypothesis of a post-treatment MAS score reduction of 0.5 points (compared to pre-treatment, from an average of 2.5 ± 0.70 SD at baseline) with an alpha value of 0.05 and power equal to 80%. (30).

According to inclusion criteria, patients should: (1) be in the age range 18–79; (2) have sustained unilateral hemorrhagic or cerebro-vascular ischemic event in sub-acute (< 6 months) or chronic (> 6 months) phase; (3) experience a functional motor deficit of the right arm (ranging from mild to severe hemiplegia or paresis); (4) have residual cognitive capabilities sufficient for the understanding of basic instructions (Mini-Mental State Examination score > 24); (5) exhibit lack of pain upon passive mobilization of the limb; (6) be able to sign an informed consent. On the contrary, patients are excluded from the study in case of: (1) unstable state of general health; (2) inability to remain in a seated position for a prolonged period (1 h or more); (3) use of a cardiac pacemaker or other active implanted medical devices; (4) passive range of motion (ROM) lower than 10 degrees. In addition, patients who received botulinum toxin injections within 3 months prior to the participation to the study or individuals who follow any additional pharmacological treatment that may alter the outcome of the study are excluded from the participation to the study. Sudden changes in subjects' health conditions, severe alterations in their psychophysical well-being or the inability to attend more than three daily consecutive sessions will lead to the exclusion from the study.

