## Discussion

The current RCT builds on a previous clinical study by Crea et al. (11) that used the NEEM for treatment of post-stroke elbow spasticity in a 2-week (10-session) robotic rehabilitation program, which successfully prevented typical increases in post-stroke spasticity, as measured via MAS and instrumented biomechanical parameters. The present study protocol seeks to further validate the results of the initial single-arm study using a randomized controlled design with a larger sample size over a longer (4-week) treatment period, further incorporating neuromuscular (EMG) activity recordings, new exercise modalities, refined biomechanical parameters, and a personally adaptive study design.

The proposed protocol extends both the previous work and the existing body of clinical literature on robotic upper limb stroke rehabilitation in several important ways. These contributions may be best understood within the framework offered by Duret et al. (40), whose review posited that effective upper limb stroke rehabilitation programs should employ repetitive, intensive, adaptive, and quantifiable therapy. These criteria are echoed in the American Stroke Association's Guidelines on Stroke Rehabilitation (13) and are all fulfilled by the current RCT, with specific focus on the treatment and assessment of elbow spasticity.

To achieve *repetitiveness*, our protocol employs joint trajectories that are first precisely repeated by the robot in a passive mobilization exercise, and then employed as target trajectories for the user to actively follow, with assistance provided *as-needed*. In this way, the delivered highly *intensive* physiotherapy is characterized by more repetitions of higher quality than can be achieved in traditional, manually assisted therapy alone. Indeed, a majority of positive effects in robotic rehabilitation studies to date have been attributed precisely to their ability to administer repetitive, intensive physiotherapy, regardless of modality (13).

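### The 30 per group is justified by a pre-to-post MAS fall within a group, while the primary question is robot versus conventional therapy; the stated 80% power carries over only if controls do not change and the relevant SD is about 0.70

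*Protocol article*

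**What the plan says.** In the protocol article, under Participants and Recruitment, the 60 patients are "randomly allocated either to the control (*n* = 30) or treatment (*n* = 30) group". The basis follows: "The sample size of each group was calculated based on the hypothesis", namely the "hypothesis of a post-treatment MAS score reduction of 0.5 points (compared to pre-treatment, from an average of 2.5 ± 0.70 SD at baseline", and this is set "with an alpha value of 0.05 and power equal to 80" percent. Sidedness is not given. The only SD is that of the baseline score.

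The question is put differently elsewhere. Objectives states efficacy relative to conventional physical therapy. Study Protocol Design describes a trial "comparing 4 weeks of RAT using the NEEM robotic elbow exoskeleton to a control group receiving a matched volume of conventional physiotherapy". Outcome Measures bases the primary conclusions on score differences between the treatment and control groups. Statistical Analysis, however, names a paired one-way ANOVA on T0 and T1 for the primary outcomes, with the Mann-Whitney test as fallback.

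**The concern.** The planning effect is measured against the patient's own baseline, while the primary comparison is measured against another arm. The two coincide only if the control arm does not move. The control here is active therapy of matched volume, so its expected change is a planning input and should be visible. It is not stated, and neither is the SD of change or the T0-T1 correlation, one of which is needed to give power for a difference in change.

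At stake is how the result is read. The 80% could be attached to the robot-versus-control comparison, which it describes only under unstated conditions. A fall within the robotic arm could also be taken as meeting the planning hypothesis, although it does not answer the primary objective.

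**Working it through.** **Inputs from the article.** Effect 0.5 MAS points, post versus pre. Baseline SD 0.70. Alpha 0.05, power 80%. 30 per arm.

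**Assumptions made here.** Two-sided test. All 60 analysed. Same SD of 0.70 at T0 and T1. T0-T1 correlation r, not given, taken as 0.3, 0.5 and 0.7. Control-arm change, not given, varied. Then:
- SD of change = 0.70 × √(2(1 − r)): 0.83 at r = 0.3, 0.70 at r = 0.5, 0.54 at r = 0.7, 0.99 at r = 0.
- Residual SD after baseline adjustment = 0.70 × √(1 − r²): 0.50 at r = 0.7.

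**Step 1. Reproduce the 30.**
- Unpaired two-sample, normal formula: n per group = 2 × (1.960 + 0.842)² × 0.49/0.25 = 30.8, so 31. By the t distribution it is 32. Power at n = 30 is 79% (normal) or 78% (t).
- Paired, r = 0: n = (1.960 + 0.842)² × 0.98/0.25 = 30.8, so 31 (33 by t).
- Paired, r = 0.5: n = (1.960 + 0.842)² × 0.49/0.25 = 15.4, so 16 (18 by t). Power at n = 30 would be 97%.

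So 30 is nearly reproduced in two ways: as a difference between two independent samples with SD 0.70, or as a paired test with uncorrelated measurements. It is not the size for a paired test at correlation 0.5. The article does not say which formula was used.

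**Step 2. Carry it to the between-arm question.** Let the robotic arm fall by 0.5 and the control arm by c. The difference is 0.5 − c. Power comes from the noncentral t with 58 degrees of freedom and noncentrality (0.5 − c) / (SD × √(2/30)).

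Change scores, SD of change 0.70 (r = 0.5):

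| Control-arm change | Between-arm difference | Power |
|---|---|---|
| worsens by 0.1 | 0.6 | 90% |
| none | 0.5 | 78% |
| improves by 0.1 | 0.4 | 59% |
| improves by 0.2 | 0.3 | 37% |
| improves by 0.25 | 0.25 | 27–28% |

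A comparison of T1 scores alone gives the same figures if the T1 SD is 0.70.

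**Step 3. Vary the correlation.**

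| Control-arm change | r = 0.3 | r = 0.5 | r = 0.7 |
|---|---|---|---|
| none | 63% | 78% | 94% |
| improves by 0.1 | 45% | 59% | 80% |

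With baseline adjustment at r = 0.7, the figure for a 0.1 control improvement is 86%. At r = 0, the paired reading that also gives 31, change-score power with unchanged controls is 49%.

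**Step 4. Smallest difference with 80% power.** By the normal formula, (1.960 + 0.842) × 0.70 × √(2/30) = 0.51; by t, 0.515. With change scores it is about 0.61 (t) at r = 0.3 and 0.40 at r = 0.7.

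**The case against.** **The calculation is not wrong.** This stands. For a true between-arm difference of 0.5 with SD 0.70, 30 per arm gives 78–79%. What is at fault is the reference point of the 0.5.

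**Zero control change may be reasonable.** The Discussion cites a randomized pilot in which elbow MAS improved significantly with robotic plus conventional therapy but not with conventional therapy alone. It also reports that the earlier single-arm study of this device "successfully prevented typical increases in post-stroke spasticity, as measured via MAS and instrumented biomechanical parameters", which implies that spasticity may rise without effective treatment. If controls worsened, power would exceed the table's 78%. So no change, or worsening, is arguable. But the sample-size statement does not give it as the assumption, a non-significant change in a 30-patient pilot does not establish zero, and preventing an increase does not by itself show a 0.5-point fall in the robotic arm.

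**A better analysis could restore power.** Partly true. A reader might infer that the design loses its 80% as soon as the control arm improves at all. The documents do not support that: at r = 0.7 a control improvement of 0.1 still leaves 80% by change score and 86% with baseline adjustment. The article gives no correlation and names no baseline-adjusted model, so neither the loss nor the rescue can be claimed outright.

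**The named analysis is itself pre-post.** Correct. The sample size therefore agrees with the paired T0-T1 test, and it would be too strong to say that the 80% answers a question found nowhere in the plan. The conflict lies between these two sections on one side and Objectives and Outcome Measures on the other.

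**A condensed article may omit detail.** True of the derivation. But the planning hypothesis is printed here, and it is not the hypothesis of the primary objective.

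**Conclusion.** The point holds as a mismatch between the effect used for planning and the effect the trial sets out to estimate. The 80% transfers approximately to the robot-versus-control comparison only if controls do not change and the SD that governs the comparison is about 0.70. At correlation 0.5, power runs from 90% to 37% as the control arm goes from worsening by 0.1 to improving by 0.2. With unchanged controls, it runs from 63% to 94% over correlations 0.3 to 0.7. Every one of these figures rests on control changes and correlations assumed here, because the article gives neither; even the SD of change of 0.70 is the baseline SD carried over at correlation 0.5. It does not follow that the trial is too small: 30 per arm may well be adequate, but the plan does not show it for its own comparison. Should-fix.

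**What to change.** Keep 30 per arm and replace the pre-post justification with a between-arm one. State the assumed robot-minus-control difference in MAS change, the assumed control-arm change with its reason, and the assumed SD of change or T0-T1 correlation, marked as an assumption because 0.70 is the baseline SD. Then give the power. For example: at an assumed correlation of 0.5, 30 per arm gives about 78% power (two-sided 5%) for a difference of 0.5 in change, and 80% for about 0.51–0.52. Add the range over plausible correlations and over control changes in both directions.

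Align Statistical Analysis so that the primary test compares change between arms, preferably adjusted for baseline, and is not a paired T0-T1 test. Otherwise the restated sample size and the named test would still disagree.

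The cost is a less favourable stated power under some assumptions, and edits to two sections. No extra patients and no change to treatment are needed.

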## Abstract

**Background:** The reliable assessment, attribution, and alleviation of upper-limb joint stiffness are essential clinical objectives in the early rehabilitation from stroke and other neurological disorders, to prevent the progression of neuromuscular pathology and enable proactive physiotherapy toward functional recovery. However, the current clinical evaluation and treatment of this stiffness (and underlying muscle spasticity) are severely limited by their dependence on subjective evaluation and manual limb mobilization, thus rendering the evaluation imprecise and the treatment insufficiently tailored to the specific pathologies and residual capabilities of individual patients.

**Methods:** To address these needs, the proposed clinical trial will employ the NEUROExos Elbow Module (NEEM), an active robotic exoskeleton, for the passive mobilization and active training of elbow flexion and extension in 60 sub-acute and chronic stroke patients with motor impairments (hemiparesis and/or spasticity) of the right arm. The study protocol is a randomized controlled trial consisting of a 4-week functional rehabilitation program, with both clinical and robotically instrumented assessments to be conducted at baseline and post-treatment. The primary outcome measures will be a set of standard clinical scales for upper limb spasticity and motor function assessment, including the Modified Ashworth Scale and Fugl-Meyer Index, to confirm the safety and evaluate the efficacy of robotic rehabilitation in reducing elbow stiffness and improving function. Secondary outcomes will include biomechanical, muscular activity, and motor performance parameters extracted from instrumented assessments using the NEEM along with synchronous EMG recordings.

**Conclusions:** This randomized controlled trial aims to validate an innovative instrumented methodology for clinical spasticity assessment and functional rehabilitation, relying on the precision and accuracy of an elbow exoskeleton combined with EMG recordings and the expertise of a physiotherapist, thus complementing and maximizing the benefits of both practices.

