Patients are recruited from across Tuscany via referral to Versilia Hospital. Once eligibility is confirmed, patients sign an informed consent and are invited for a traditional assessment session with a therapist blinded to their group assignment. Afterwards, patients are randomly allocated to either arm via a random number generator algorithm in blocks of ten. Patients perform daily rehabilitation therapy (5 sessions per week) for 30 min over a 4-week period, for a total of 20 treatment sessions. Subjects assigned to the control group perform 30 min of conventional therapy exercises; patients assigned to the treatment group are subject to 30 min of treatment with the elbow exoskeleton.

Subjects in both groups will undergo both clinical and instrumented evaluations (using the NEEM device) at two time points: pre-treatment (baseline, session T0) and post-treatment (session T1) within 1 week after the end of treatment. Each clinical assessment will include the evaluation of MAS and FMA scores, assessed in blinded fashion. All robotic assessments will include the evaluation of the elbow ROM, as well as other biomechanical and electromyography parameters extracted under different dynamic conditions. Figure 1 represents a scheme of the experimental protocol.

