### Statistical Analysis

In addition to descriptive statistics characterizing the study population and the assessment of potential clinical or demographic differences between groups via Pearson's chi-squared test, this study will employ a paired one-way analysis of variance (ANOVA) of all primary outcome measures, with repeated measures taken from baseline (T0) and post-treatment (T1). This series of tests will be contingent on confirmation of the normality of all data distributions using the Shapiro-Wilk normality test. If data are found not to conform to the null hypothesis of Gaussian distribution, then the parametric Mann–Whitney *U*-test (also known as Wilcoxon rank sum test) will be used in place of ANOVA, in pair-wise fashion.

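### Sub-acute and chronic patients are pooled, but neither the allocation nor the analysis as described allows for phase, which costs precision on MAS

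*Protocol article*

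**What the plan says.** All places are in the Protocol article.

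- **Eligibility.** Participants and Recruitment requires patients to "have sustained unilateral hemorrhagic or cerebro-vascular ischemic event in sub-acute (< 6 months) or chronic (> 6 months) phase". The Abstract counts "60 sub-acute and chronic stroke patients with motor impairments" in one trial. No quota or expected split is given.
- **Allocation.** Participants and Recruitment says that "patients are randomly allocated to either arm via a random number generator algorithm in blocks of ten", with patients "randomly allocated either to the control (*n* = 30) or treatment (*n* = 30) group". No stratification factor is named. The FMA cut at 28 (Study Protocol Design) sets the exercise level inside the robotic arm; it is not a randomisation stratum.
- **Hypothesis.** The sample size rests on the "hypothesis of a post-treatment MAS score reduction of 0.5 points", "from an average of 2.5 ± 0.70 SD at baseline", with alpha 0.05 and 80% power.
- **Analysis.** Statistical Analysis plans a "paired one-way analysis of variance (ANOVA) of all primary outcome measures, with repeated measures taken from baseline (T0) and post-treatment (T1"), with Mann-Whitney if normality fails. Baseline differences are tested by chi-squared, with no stated consequence.
- **Comparison.** Outcome Measures says that score differences between the two groups will be analysed.
- **Natural course.** The Discussion describes the earlier single-arm study of the device as one "which successfully prevented typical increases in post-stroke spasticity, as measured via MAS and instrumented biomechanical parameters". The Introduction makes the same point.

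**The concern.** If spasticity tends to rise after stroke, time since stroke is a plausible predictor of four-week MAS change in either arm. Phase is known before allocation, because it is part of the eligibility check. A predictor that is neither balanced nor modelled stays in the error term, and in a trial of 60 the arms can differ on it by chance. The planned size leaves no spare power to absorb that.

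The hypothesis wording adds to the difficulty. A pre-to-post fall of 0.5 points describes success where spasticity is stable. Where it would otherwise rise, success is a smaller rise. Only a between-arm statement covers both.

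**Working it through.** **1. The plan's own figure.** Inputs from Participants and Recruitment: difference 0.5, SD 0.70, alpha 0.05 (taken as two-sided), power 80%.

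n per group = 2 × (1.960 + 0.842)² × 0.70² / 0.5² = 30.8, so 31. The stated 30 is reproduced to within one patient. At 30 per group the standard error is 0.70 × √(2/30) = 0.181, and power is Φ(0.5/0.181 − 1.960) = 0.790 (0.776 with the t distribution).

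**2. Chance imbalance.** Let K of 60 patients be sub-acute, with 30 per arm and no stratification. The number in one arm is hypergeometric, and blocks of ten do not change this when phases arrive in random order. A gap of 20 percentage points is 6 patients. The share is an assumption, since the article gives none.

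| Sub-acute share | K | SD of the difference in share | P(difference ≥ 20 points) |
|---|---|---|---|
| 20% | 12 | 0.104 | 10.4% |
| 30% | 18 | 0.119 | 15.8% |
| 50% | 30 | 0.130 | 19.6% |

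If the number of sub-acute patients itself varies at random around one half, the last figure is about 15%.

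**3. Effect on the MAS contrast.** Let g be the difference between phases in mean MAS change, in either arm (assumed). A 20-point imbalance shifts the contrast by 0.20 × g.

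**4. Effect on power at 30 per group.** With p the sub-acute share, the phase gap contributes p(1−p)g² to the variance. There are two readings of the 0.70, which the article does not settle:

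- Reading A: 0.70 is the SD within a phase, so pooling raises it to √(0.49 + p(1−p)g²).
- Reading B: 0.70 already includes the phase gap, so adjustment lowers it to √(0.49 − p(1−p)g²).

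Ranges are for p = 0.3 to 0.5.

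| g | Shift at 20 points | Share of 0.5 target | A: SD, n per group, power | B: SD after adjustment, power |
|---|---|---|---|---|
| 0.25 | 0.05 | 10% | 0.709–0.711, 32, 0.777–0.779 | 0.689–0.691, 0.801–0.803 |
| 0.5 | 0.10 | 20% | 0.737–0.743, 35, 0.741–0.748 | 0.654–0.661, 0.833–0.842 |
| 1.0 | 0.20 | 40% | 0.837–0.860, 44–47, 0.615–0.639 | 0.490–0.529, 0.955–0.977 |

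Steps 3 and 4 show the same variance in two ways, so they should not be added together.

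**5. Would the baseline test catch it?** For 18/30 against 12/30 sub-acute, chi-squared = 60 × (18×18 − 12×12)² / 30⁴ = 2.4, p ≈ 0.12. The planned check would not flag a 20-point imbalance at the 5% level, and it leads to no adjustment in any case.

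**The case against.** The strongest reply is that this is a condensed article. It gives allocation in one sentence and analysis in one paragraph, and it never says outright that allocation is unstratified or that no covariate will be used. A full protocol or analysis plan may add both. That is fair, and the point is therefore limited to the method as described. But the Statistical Analysis section does name a specific model and a specific fallback, and a plain Mann-Whitney test cannot carry a covariate.

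Several stronger readings are tempting and do not stand:

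- *That the trial is biased.* Randomisation keeps the between-arm estimate unbiased on average, and a valid unadjusted between-arm test keeps its type I error with chance imbalance included.
- *That pooling hides benefit seen as prevented worsening.* Outcome Measures plans a between-group comparison, in which a smaller rise already counts as benefit. The difficulty lies in the pre-to-post hypothesis wording and in any within-arm reading of the ANOVA.
- *That spontaneous change in sub-acute patients rivals the treatment effect, or distorts FMA by some number of points.* The article gives no rate by phase, does not say which phase shows the rise, and gives no spontaneous course for FMA. Nor is either arm untreated.
- *That enrolling both phases is an error.* It is a legitimate choice.

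It also stands that under reading B pooling costs none of the planned power, so adjustment is purely a gain. And the Ethics Statement speaks of consent in the past tense, so allocation may already have begun and stratification may no longer be possible.

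**Conclusion.** The point holds as one of precision. The article pools two phases, names no phase stratum, and states an analysis without phase or baseline score, in a trial whose 30 per group gives about 78–79% power. The size depends on two quantities that the article does not give: the phase mix and the phase gap in MAS change. For shares of 20%, 30% and 50%, a 20-point imbalance or worse arises in about 10%, 16% and 20% of trials. At a gap of 0.25 MAS points the consequence is negligible. At 0.5, that imbalance moves the contrast by a fifth of the target, and power is 74–75% under reading A, or could be raised to 83–84% under reading B. No size can be put on the effect for FMA. The remedy costs little, so the change is worth making even though the gap is unknown.

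**What to change.** 1. In place of the paired one-way ANOVA, compare T1 MAS and T1 FMA between arms with the baseline score and phase (or log time since stroke) as covariates.
2. If a rank-based fallback is needed, name one that allows for phase, such as a stratified rank test.
3. If allocation has not begun, stratify the list by phase and use smaller blocks, because incomplete blocks of ten within strata can undo the balance. If it has begun, leave allocation alone and rely on item 1.
4. Assign exactly 6 months to one stratum; as written it falls in neither phase.
5. State the MAS hypothesis as a between-arm difference in change, in line with Outcome Measures.

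Cost: one or two degrees of freedom, one field in the randomisation list, and no extra patients or visits. It does mean replacing the stated model and its fallback, not merely adding a term.

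### Removing randomised patients from the study, not only from further sessions, leaves a completer comparison that can be biased if removals differ by arm

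*Protocol article*

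**What the plan says.** The last sentence on eligibility in the protocol article (Participants and Recruitment) gives three reasons for removing a patient. Two concern health: "Sudden changes in subjects' health conditions, severe alterations in their psychophysical well-being". The third concerns attendance: "the inability to attend more than three daily consecutive sessions will lead to the exclusion from the study". In all three cases the patient leaves the study, and the sentence does not separate this from stopping the sessions.

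The same section gives the order of events. Eligibility, consent and the baseline clinical assessment come first. Then: "Afterwards, patients are randomly allocated to either arm via a random number generator algorithm in blocks of ten". Treatment follows: "Patients perform daily rehabilitation therapy (5 sessions per week) for 30 min over a 4-week period, for a total of 20 treatment sessions". Both groups "undergo both clinical and instrumented evaluations (using the NEEM device) at two time points": baseline, and "post-treatment (session T1) within 1 week after the end of treatment". Statistical Analysis bases the primary analysis on the T0 and T1 measurements, and Outcome Measures compares score differences between the two groups. Nothing in the article keeps a removed patient under follow-up or in the analysis.

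**The concern.** Missed sessions can occur only after allocation, and a health change or a loss of well-being may occur then too. Such events may be related to prognosis and to how well the assigned treatment is tolerated, and the treatments differ (exoskeleton against manual mobilisation).

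Study Protocol Design describes a "single-blind randomized controlled trial comparing 4 weeks of RAT using the NEEM robotic elbow exoskeleton". The clinical assessors are blinded, but patients and treating therapists necessarily know the arm. The health triggers have no objective threshold, so their use is a matter of judgement by people who may know the allocation.

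If removed patients have no T1 scores, the comparison is of completers with completers. Randomisation no longer guarantees that the groups being compared are alike. There is no intermediate visit for MAS or FMA to represent those who left, so the data could not show whether the losses were harmless. A later choice of analysis set cannot recover outcomes that were not collected.

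**Working it through.** **Can the triggers act after randomisation?** The attendance trigger refers to daily sessions. All 20 sessions come after allocation, so this trigger acts only after it. The health triggers carry no time limit: they can act after allocation, but the text does not say that they do so exclusively.

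**The plan's sample size.** Participants and Recruitment gives a 0.5-point MAS reduction, SD 0.70, alpha 0.05, power 80% and 30 patients per arm. Read as a two-sided, two-sample comparison:

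n per arm = 2 × (1.960 + 0.842)² × 0.70² / 0.5² = 30.8, so 31 (32 by the t test).

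This is within 2 of the stated 30 and leaves no allowance for loss. The wording itself describes a change from pre-treatment. A paired calculation gives 24, 18 or 12 for assumed correlations of 0.3, 0.5 or 0.7, and does not reproduce 30.

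**Bias, closed form.** Let f_T and f_C be the fractions removed in each arm. Let removed patients be g MAS points worse than completers in both arms, with no true difference between arms. Each completer mean is too favourable by f × g, so the bias in the difference is (f_T − f_C) × g. Rates and g are assumptions.

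| Removed, robot v control | g = 0.5 | g = 1.0 |
|---|---|---|
| 10% v 10% | 0; two-sided error 5.0% | 0; 5.0% |
| 20% v 10% | 0.10 × 0.5 = 0.05; 5.7% | 0.10 × 1.0 = 0.10; 8.0% |
| 20% v 0% | 0.20 × 0.5 = 0.10; 8.2% | 0.20 × 1.0 = 0.20; 18.1% |

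**Bias, simulation.** 30 patients per arm, improvement distributed N(0.3, 0.7) in both arms, two-sided t test at 5%. The patients removed are those lowest on improvement plus N(0, 0.7) noise, so the removal score correlates 0.7/√(0.7² + 0.7²) = 0.71 with improvement. The nominal chance of a false result favouring the robot is 2.5%.

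| Lost, robot v control | Bias (MAS points) | False result favouring the robot |
|---|---|---|
| 3 v 3 | 0.00 | about 3% |
| 4 v 2 | about 0.05 | about 5.5% |
| 5 v 3 | about 0.05 | about 6% |
| 3 v 0 | 0.09 | about 8% |
| 5 v 0 | 0.14 | about 12% |
| 3 v 0, correlation about 0.32 | not quoted | about 4% |
| 5 v 0, correlation about 0.32 | not quoted | about 5% |
| 3 v 0, loss unrelated to outcome | about 0 | 2.5% |

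Against the 0.5-point target, 0.09 and 0.14 are 0.09/0.5 = 18% and 0.14/0.5 = 28%.

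**Power.** On the two-sample reading (t test, 0.5 points, SD 0.70), power is 77.6% at 30 per arm, 73.1% at 27 (10% lost) and 67.8% at 24 (20% lost).

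**The case against.** A reader might infer that the rule does drop outcomes selectively by arm and so undoes the randomised comparison. The document does not support that. The rule is worded identically for both arms and no removal rates are given. If similar patients are lost equally, the bias in the difference is about zero. Selective loss is a risk, not a documented fact, and this objection stands.

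A reader might also quote the 8% and 12% error rates as the expected effect. They assume losses in the robot arm only and a correlation of 0.71 that nothing in the document supports. The triggers are illness, well-being and attendance, not MAS response. With a weaker link, or losses in both arms, the figures are much smaller.

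That T1 data are lost is an inference. The article names no analysis set and no rule for missing data, and a full protocol or SAP that is not shown could keep these patients. This is a fair caution, but leaving the study before the only outcome visit is most naturally read as having no outcome. The point rests on this stated rule, not on a missing intention-to-treat statement.

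The health triggers are weaker evidence than the attendance trigger, because they are not tied to the time after allocation. The power loss is secondary: any dropout causes it, and it depends on reading the sample size as a two-sample calculation.

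**Conclusion.** The concern holds as a risk. The article removes randomised patients from the study for an event that can occur only after allocation, and for health events that may. On the natural reading they have no primary outcome, and the comparison is among completers. It is biased only if removals differ by arm in number or prognosis. That is possible because the treatments differ, the arm is known to patients and therapists, and the health triggers need judgement.

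The size cannot be read from the document. On the assumptions shown, it runs from about zero, through about 0.05 MAS points for modest imbalance, to 0.09 to 0.14 points for 3 to 5 poorer responders lost from the robot arm only. Losses of 10% to 20% would also lower power from about 78% to between 73% and 68%, even if balanced. Balance cannot be assumed in advance, and without T1 scores on those who left it could not be checked afterwards.

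**What to change.** Leave the rule for stopping sessions to the clinicians, and change only its consequence: replace removal from the study with discontinuation of study sessions. Then state that:

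- every randomised patient who remains willing and able is invited to the T1 MAS and FMA assessment regardless of attendance;
- for patients who stop early, T1 falls at the originally scheduled time, within 1 week after the planned end of the 4-week period, so that timing is the same for all;
- all patients are analysed in the arm to which they were randomised, with a completer analysis as sensitivity;
- discontinuations and their reasons are reported by arm.

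The cost is a few sentences in the protocol and some extra effort to bring patients to a visit that is already planned. Some T1 scores will come from partly treated patients, which dilutes the effect of full treatment somewhat; the completer analysis shows by how much the two estimates differ.
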